We will recruit 480 youth from the 40 secondary schools randomized to receive the YRI delivered with mobile supervision and 480 youth from schools that will receive YRI delivered with standard supervision. We will enroll 240 youth from 10 control schools. We will aim to recruit 24 youth per school, with two YRI groups per intervention school. We aim to recruit an equal number of male and female participants, as the YRI is delivered in separate groups for males and females. The target sample size of 1200 youth is powered to account for 10–20% attrition per our prior experience in Sierra Leone. Youth inclusion criteria are: (a) currently enrolled in a secondary school in the Western region; (b) male or female aged 14–24; (c) able and willing to attend an extracurricular school activity. Parental consent and youth assent will be obtained for all youth under age 18.

Our target age for enrollment of youth (aged 14–24) is based on prior research on the YRI demonstrating that the intervention is effective with male and female populations within this age range [19, 20]. Including students 18–24 reduces potential bias towards those youth who take longer to complete secondary school, delayed entry into school, or dropped out of school and later returned. Excluding students older than age 24 ensures we are targeting the developmental window of youth as defined by the United Nations and the World Health Organization.

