#### Statistical power analysis for fidelity to YRI implementation

To assess the minimal detectable effect size for the two-tailed null hypothesis of no difference for fidelity of groups receiving mobile versus standard supervision requires an estimate of the within-group ICC for fidelity for which there is no clear guidance in the literature. Given our standard assumptions, at a small to medium ICC of 0.2 for a two-tailed test with a null hypothesis of no difference for 80 groups and 12 fidelity ratings, the minimum detectable effect size would be 0.30, while at a large ICC of 0.5 the minimum detectable effect size would be 0.41.

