#### Statistical power analysis for student outcomes

Power will be sufficient to assess our secondary aim and examine the hypothesis that the YRI delivered by teachers participating in mobile supervision will be noninferior in terms of youth mental health outcomes compared to the YRI delivered by teachers receiving standard supervision. At a power of 0.8 and an alpha of *p* <.05 (one-tailed to assess noninferiority), using an ICC of 0.03 (based on prior ICCs for mental health outcomes of 0.01-0.04) [18] for the group for comparisons at a single time point (post-intervention or 12-month follow-up) for student outcomes, the minimal detectable standardized effect size for a standardized difference (d) between the two of 0.21; in other words, at a negative difference of 0.21 or smaller, mobile supervision will be considered noninferior to standard. To test individual null hypotheses that either YRI implementation model (20 schools per YRI supervision mode) is superior (one-tailed) to the 10 untreated control schools with regard to mental health or educational outcomes, we have 0.8 power to detect a standardized effect of 0.26. In a comparison of all 40 YRI schools as compared to the 10 control schools, the minimum detectable effect would be 0.21.

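### Superiority of the YRI over untreated control is tested one-tailed with no reason given for setting harm aside, and the detectable effects of 0.26 and 0.21 do not share one basis

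*Protocol article*

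**What the plan says.** The section on power for student outcomes opens with mobile versus standard supervision: "At a power of 0.8 and an alpha of *p* <.05 (one-tailed to assess noninferiority"). It takes the clustering from prior work, "using an ICC of 0.03 (based on prior ICCs for mental health outcomes of 0.01-0.04"), and describes that ICC as applying to the group. It gives 0.21 as the detectable difference and noninferiority bound.

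It then turns to untreated control. The comparison concerns "either YRI implementation model (20 schools per YRI supervision mode"), and the claim to be tested for each arm is worded with a single tail: "is superior (one-tailed) to the 10 untreated control schools with regard to mental health or educational outcomes, we have 0.8 power to detect". The effect given is 0.26. Alpha is not restated and no reason is given for the single tail. For all 40 YRI schools against the 10 control schools, the section gives 0.21 without stating sidedness.

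On cluster size, Settings and participants says: "We will aim to recruit 24 youth per school, with two YRI groups per intervention school". The same section says that the sample allows for 10 to 20% attrition. The quantitative analysis section says both YRI models can be compared with control but sets no sidedness for that. The fidelity power statement is "for a two-tailed test with a null hypothesis of no difference for 80 groups and 12 fidelity ratings".

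**The concern.** A single tail is natural for noninferiority, where only one direction matters to the decision. That reason does not carry over to YRI against no YRI, where a difference in either direction would matter.

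The article offers no ground for excluding an adverse effect in this setting. Delivery is by newly trained teachers. Youth are eligible if enrolled in a secondary school in the region, aged 14 to 24 and "able and willing to attend an extracurricular school activity", with no symptom criterion. The outcomes named for this test include schooling as well as mental health. The earlier evidence in the Background comes from an alternative education programme and an employment programme.

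Two things are at stake. Benefit of the teacher-delivered YRI could be claimed on weaker evidence than a conventional test demands. If symptoms or schooling worsened, the planned test could report only a failure to show superiority.

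**Working it through.** **Inputs from the article.** Power 0.80; ICC 0.03; 20 schools per YRI arm and 10 control schools; 24 youth per school; two YRI groups per intervention school, so about 12 per group; attrition 10 to 20%. One-sided alpha 0.05 for superiority is inferred from the noninferiority sentence.

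**Assumption.** Control schools have no YRI groups. The group-level calculation treats each as two clusters of 12.

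**Error rates with no YRI effect, one test.**
- One-sided 0.05: false benefit 0.05, false harm 0, total 0.05.
- Two-sided 0.05: false benefit 0.025, false harm 0.025, total 0.05.

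**Formula.** Detectable effect = (z for alpha + z for power) × SE, where SE = sqrt{[1 + (m − 1) × ICC] / m × (1/k1 + 1/k2)}. Here m is the cluster size and k1, k2 are the numbers of clusters. The multiplier is 1.6449 + 0.8416 = 2.4865 one-sided and 1.9600 + 0.8416 = 2.8016 two-sided.

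**Reproducing the stated 0.26 (one arm versus control, no attrition).**
- Schools of 24, 20 v 10: SE = sqrt(1.69/24 × 0.15) = 0.1028. One-sided 0.256, two-sided 0.288.
- Groups of 12, 40 v 20: SE = sqrt(1.33/12 × 0.075) = 0.0912. One-sided 0.227, two-sided 0.255.

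So 0.26 comes out one-tailed with school clusters, or two-tailed with group clusters. The text labels it one-tailed but places the ICC at the group. One-tailed with groups, it reaches only 0.247 even at 20% attrition.

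The mobile versus standard 0.21 does not settle the matter. It is 0.209 one-tailed with schools and 0.209 two-tailed with groups.

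**Two-sided values, single arm.** With 20% attrition, m becomes 19.2 or 9.6.
- Schools: SE = sqrt(1.546/19.2 × 0.15) = 0.1099, giving 0.308.
- Groups: SE = sqrt(1.258/9.6 × 0.075) = 0.0991, giving 0.278.

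| Cluster | Attrition | One-sided | Two-sided | Two-sided power at 0.26 |
|---|---|---|---|---|
| School, 24 | 0% | 0.256 | 0.288 | 0.716 |
| School, 24 | 20% | 0.273 | 0.308 | 0.658 |
| Group, 12 | 0% | 0.227 | 0.255 | 0.814 |
| Group, 12 | 20% | 0.247 | 0.278 | 0.746 |

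**Pooled YRI versus control, no attrition.**
- Schools, 40 v 10: SE = sqrt(1.69/24 × 0.125) = 0.0938. One-sided 0.233, two-sided 0.263.
- Groups, 80 v 20: SE = sqrt(1.33/12 × 0.0625) = 0.0832. One-sided 0.207, two-sided 0.233.

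The stated 0.21 fits only the one-sided group calculation, and that calculation gives 0.227 for the single arm, not 0.26.

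**Consistency.** If sidedness, ICC, cluster level and attrition are the same, the ratio of single-arm to pooled detectable effect depends only on the cluster counts: sqrt(0.15/0.125) = 1.095. The stated ratio is 0.26/0.21 = 1.238. Rounding allows 0.255/0.215 = 1.19 to 0.265/0.205 = 1.29, which still excludes 1.095.

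**The case against.** Youth clinical outcomes are secondary. The Study design section says control schools are there mainly for the cost-effectiveness analysis, and none of the four listed hypotheses tests youth mental health in YRI against control. The one-tailed label appears only in the power section. Multilevel models with arm indicators give signed estimates, so a worsening would be visible even if not formally declared. Prior benefit of the YRI is reported, and a directional test against untreated control is a recognised choice. A separate analysis plan may set the operative test. All this lowers the weight of the point. It does not remove it: the article states the single tail and does not offer the earlier results as its reason.

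Several stronger readings are tempting and are not supported:
- A reader might infer that the false-positive rate doubles. Only false claims of benefit double.
- A reader might infer that the true two-sided figure is 0.29 with power at 0.26 down to 70%. Taking the one-tailed label at face value gives 0.26 × 2.8016/2.4865 = 0.293 and that power. The arithmetic equally allows 0.26 to be a two-sided figure under group clustering, the level the text names.
- A reader might rescale the pooled figure by the same factor of 1.127, to 0.237. That keeps its inconsistency; the school-level model gives 0.263.
- A reader might cite the chance of at least one of two arms being falsely declared superior. With a correlation of 2/3 from the shared control, it is 8.2% at one-sided 0.05. Part of that is two-arm multiplicity, a separate question, and the article speaks of individual hypotheses.
- A reader might see a contradiction with the two-tailed fidelity test. That is a no-difference question between two supervision modes, so there is none.

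**Conclusion.** The point holds as a correctable weakness in a secondary comparison. Superiority over untreated control is stated as one-tailed without a reason. If the .05 carries over, which is inferred and not written for this test, a claim of benefit is allowed at 5% where convention allows 2.5%, and harm cannot be declared.

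The effect on the detectable difference depends on a cluster level that the article leaves ambiguous. Two-sided, it is 0.29 to 0.31 for schools or 0.26 to 0.28 for groups over 0 to 20% attrition. Whatever the sidedness, the stated 0.26 and 0.21 for the two control comparisons cannot come from one set of assumptions. These results rest on ICC 0.03, equal cluster sizes, normal quantiles and, for the group calculation, control youth clustered in twelves.

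**What to change.** In the power section for student outcomes, and in the quantitative analysis section to match:
- Test each YRI model and the pooled YRI arms against control two-sided at 0.05, with 95% confidence intervals. One-sided 0.025 gives the same protection against a false claim of benefit, and the interval would then show any worsening.
- Keep one-sided testing for mobile versus standard noninferiority only.
- State the alpha for the control comparisons, whether the ICC of 0.03 belongs to the school or the YRI group, and the attrition assumed.
- Recompute the single-arm and pooled detectable effects on that one basis. With no attrition the two-sided values are about 0.29 and 0.26 for schools, or 0.26 and 0.23 for groups.

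The cost is wording and slightly less favourable stated detectable effects. No schools or youth are added. The article reports that youth recruitment had not begun when it was submitted.

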### Study design

We will conduct a hybrid type 3 implementation-effectiveness cluster-randomized trial design [25] to investigate mobile-based supervision of YRI delivery by teachers in Sierra Leone’s secondary schools as a new implementation strategy, with clinical outcomes of the YRI on youth mental and behavioral health as secondary outcomes. We will use a mixed methods approach to investigate study aims. The Exploration, Preparation, Implementation, Sustainment (EPIS) framework [26], a broad, context sensitive implementation science process model, will guide study implementation. Randomization to study condition will occur at the level of the school. Schools (*n* = 50) will be randomized to YRI with mobile-based supervision (*n* = 20 schools/*n* = 480 youth), YRI with standard (in-person) supervision (*n* = 20 schools/*n* = 480 youth) or control (*n* = 10 schools/*n* = 240 youth). Control schools are necessary primarily for the cost-effectiveness analysis because they will provide reference level estimates of QALYs gained by intervention schools. We selected an unequal randomization design to reduce the number of youths who are exposed to the waitlist control [27]. We will offer YRI training to interested teachers in control schools following 12-month follow-up data collection. To optimize comparability between schools, we will match schools into quintets using an algorithm prior to randomly assigning two members of each quintet to each supervision model and the fifth to the control. All research assistants and data analysts will be blinded to participant assignment and will assign schools to study condition based on the allocation sequence.

Regarding standard reporting, this study will adhere to the Standard Protocol Items: Recommendations for Intervention Trials (SPIRIT) guidelines (See Fig. 2) and the Consolidated Standards of Reporting Trials (CONSORT). This trial is registered with the Clinical Trials Registry maintained by the National Library of Medicine at the National Institute of Health (Trial ID: NCT05737667; registered on 02/02/23). This study is approved by the Brown University Institutional Review Board (Protocol #2,022,003,442) and the Sierra Leone Ethics and Scientific Review Committee. Any subsequent modifications will be reviewed by both of these review committees for approval and then submitted to the Clinical Trials Registry as an amendment. The study protocol was also eviewed as part of the funding application.

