### Data analysis

#### Quantitative analysis

We will compare fidelity trajectories of teachers receiving mobile supervision to those of teachers receiving standard supervision and investigate the null hypothesis that mobile supervision will not differ from standard supervision. We will conduct exploratory analyses to uncover typical trajectories for each supervision method (mobile-based or standard) and undertake comparisons using growth curve modeling by means of multilevel models [44]. We will use HLM software (v.8.2), which estimates multiple imputations based on the dependencies of multilevel data. Missing time points are addressed by the multilevel approach to growth modeling, and data from all enrolled participants can be analyzed in accordance with our intention to treat design. The null hypothesis is that the outcomes for the mobile supervision YRI groups will not differ from those in standard supervision YRI groups. With this approach, we can compare both YRI models (as identified by dummy variables) to the untreated control group or assess the null hypothesis of no difference between the fidelity in the two models (mobile-based vs. standard supervision).

We will also investigate the null hypothesis that mobile supervision will not differ from standard supervision at post-intervention in youth outcomes. To investigate YRI effects on mental health among youth at post-intervention, we will use multilevel models to accommodate the clustering of students within YRI groups. For analysis of student outcomes, student characteristics will be modeled in a level-one equation. The group characteristics will be modeled in the level-two equation. School characteristics will be incorporated into a third level.

However, we do not expect a significant school-level intraclass correlation (ICC) for targeted YRI outcomes. In the event we do not find a significant ICC, sector and rural/urban will be represented in the group-level equation, and a two-level model will be estimated.

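### The three youth detectable effects (0.21, 0.26 and 0.21) cannot share one clustering basis, and at the planning ICC of 0.03 they are not all delivered after the 10–20% attrition the protocol says it covers

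*Protocol article*

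**What the plan says.** In the protocol article, Settings and participants sets 24 youth per school, with two YRI groups in each intervention school, and states: "The target sample size of 1200 youth is powered to account for 10–20% attrition per our prior experience in Sierra Leone".

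Statistical power analysis for student outcomes fixes the inputs: "At a power of 0.8", "alpha of *p* <.05 (one-tailed to assess noninferiority") and "using an ICC of 0.03 (based on prior ICCs for mental health outcomes of 0.01-0.04) [18] for the group". From these it states three detectable standardised effects:

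- 0.21 for mobile against standard supervision. This is also the noninferiority criterion: "at a negative difference of 0.21 or smaller, mobile supervision will be considered noninferior to standard".
- 0.26 for either YRI arm (20 schools) against the 10 control schools: "we have 0.8 power to detect a standardized effect of 0.26".
- 0.21 for all 40 YRI schools against the 10 control schools.

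Study design says: "Randomization to study condition will occur at the level of the school". Quantitative analysis clusters students within YRI groups, with school as a third level. It adds that "we do not expect a significant school-level intraclass correlation (ICC) for targeted YRI outcomes" and allows a two-level student and group model if none is found.

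**The concern.** A reader of the two sections would take 0.21, 0.26 and 0.21 to be what the trial can detect after 10–20% of youth are lost. The power section does not tie the figures to an analysed number, and two features suggest that they do not all carry the allowance. First, the 20 v 20 and 20 v 10 figures come out at full enrolment if the ICC is applied to the randomised school. Second, the 40 v 10 comparison has the same detectable effect as the 20 v 20 comparison, although its variance is larger.

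Two things are at stake. The first 0.21 is also the noninferiority margin, so any shortfall reduces the chance of concluding noninferiority when the arms are truly equal. The second 0.21 is the stated sensitivity of the overall YRI against control comparison of youth outcomes.

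**Working it through.** **Inputs.** One-sided alpha 0.05 and power 0.80, so the multiplier is 1.645 + 0.842 = 2.487; ICC 0.03 (all from the power section). Schools 20, 20 and 10, with 24 youth each; two groups per intervention school, so about 12 per group; loss of 10–20% (Study design; Settings and participants).

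**Formulas.** Design effect DE = 1 + (m − 1) × 0.03, where m is the analysed cluster size. SE = √[DE × (1/n1 + 1/n2)]. Detectable effect = 2.487 × SE. Power at a stated effect d = Φ(d/SE − 1.645). Attrition shrinks both m and n.

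**Step 1: the plan's figures at full enrolment, school as cluster.** m = 24, DE = 1 + 23 × 0.03 = 1.69.

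- 20 v 20: SE = √[1.69 × (1/480 + 1/480)] = 0.0839, giving 0.209. Stated 0.21: reproduced.
- 20 v 10: SE = √[1.69 × (1/480 + 1/240)] = 0.1028, giving 0.256. Stated 0.26: reproduced.
- 40 v 10: SE = √[1.69 × (1/960 + 1/240)] = 0.0938, giving 0.233. Stated 0.21: not reproduced.

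**Step 2: the same at group level.** m = 12, DE = 1 + 11 × 0.03 = 1.33. The results are 0.185, 0.227 and 0.207. Here only the pooled figure matches.

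**Step 3: add attrition.** At school level, m is 21.6 or 19.2 (DE 1.618 or 1.546). At group level, m is 10.8 or 9.6 (DE 1.294 or 1.258). Analysed numbers are 432 or 384 per YRI arm and 216 or 192 controls. Power, in brackets, is at the stated effect.

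| Comparison (stated) | School, 0% | School, 10% | School, 20% | Group, 0% | Group, 10% | Group, 20% |
|---|---|---|---|---|---|---|
| 20 v 20 (0.21) | 0.209 (80.4%) | 0.215 (78.3%) | 0.223 (75.7%) | 0.185 (88.0%) | 0.193 (85.7%) | 0.201 (82.9%) |
| 20 v 10 (0.26) | 0.256 (81.2%) | 0.264 (79.0%) | 0.273 (76.5%) | 0.227 (88.6%) | 0.236 (86.4%) | 0.246 (83.6%) |
| 40 v 10 (0.21) | 0.233 (72.4%) | 0.241 (70.0%) | 0.249 (67.3%) | 0.207 (81.0%) | 0.215 (78.3%) | 0.225 (75.0%) |

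**Step 4: can both values of 0.21 be right?** With the same cluster size, ICC and loss in every arm, DE cancels from the ratio of the 40 v 10 effect to the 20 v 20 effect. That ratio is √[(1/40 + 1/10)/(1/20 + 1/20)] = √(0.125/0.10) = 1.118. If the 20 v 20 effect rounds to 0.21, it is at least 0.205, and the 40 v 10 effect is then at least 0.205 × 1.118 = 0.229. This holds at any common ICC, level or attrition. The two figures therefore come from different bases, or one is wrong.

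**Step 5: how much the group basis depends on independent groups within a school.** With group ICC 0.03, 20% loss and a correlation r between youth in the two groups of one school, DE becomes 1 + 8.6 × 0.03 + 9.6r. Power at 0.21 for 20 v 20 is 82.9% at r = 0, 80.4% at r = 0.010 and 79.9% at r = 0.012. At r = 0.03 it is 75.7%, the school-level result.

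**The case against.** The strongest reply is that the protocol assigns the ICC of 0.03 to the group, expects no significant school-level ICC and plans a two-level fallback model. On that basis 0.21 and 0.26 hold at 20% loss, with 83–84% power. One can even reproduce both with attrition included. If the planned design effect of 1.33 is kept, 20% is then removed (384 v 384 and 384 v 192), and t quantiles on schools minus two degrees of freedom are used, the results are 0.211 and 0.260.

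That part stands. A reader might infer from the school-level match that the figures were computed with no attrition and that the sample is therefore not powered for it. The documents do not support so much. They nowhere apply 0.03 to schools, a second account fits the same two figures, and even at school level 10% loss costs only one to two points of power, with 0.264 still rounding to 0.26.

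The reply has three limits. It needs a correlation between groups in the same randomised school below about 0.012, whereas the ICC range the protocol quotes is 0.01–0.04. It gives control schools groups that Settings and participants describes only for intervention schools. And it does not rescue the pooled figure, which at group level is 0.215–0.225 after loss. The convention that returns 0.211 and 0.260 gives 0.235 for 40 v 10.

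It is also fair that a condensed article may leave the cluster unit and analysed number to a fuller document, so their absence is not the point here. The point is that the stated figures conflict with one another and with the attrition claim.

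**Conclusion.** The point holds in a limited form. At ICC 0.03 the three stated effects are not all delivered after 10–20% attrition on either clustering basis.

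- **Pooled comparison (40 v 10).** This is the firm part. The stated 0.21 has 78–75% power after loss on the favourable group basis and 70–67% at school level. It also cannot coexist with 0.21 for 20 v 20 on a common basis.
- **Mobile v standard, and one YRI arm v control.** These are conditional. If 0.03 applies to the randomised school, power after 10–20% loss is 78–76% at 0.21 and 79–77% at 0.26. If it applies to groups of 12 with no school-level correlation, both are covered.

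The results assume equal cluster sizes, normal quantiles and no gain from matching or covariates, since the power section claims none. They also depend on the ICC. At 0.01, the bottom of the quoted range, all three figures would hold at group level with 20% loss (pooled effect 0.209). At 0.04 the pooled shortfall is larger (0.233 at group level). The shortfall is modest and concerns secondary outcomes. It calls for corrected figures and does not show that the trial is too small.

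**What to change.** Recompute all three figures in the student power section on one stated basis, naming the cluster unit, the analysed number per arm and the attrition assumed. Either of these would do:

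- **Report after attrition, with the school as cluster:** about 0.22 for 20 v 20, 0.26–0.27 for 20 v 10 and 0.24–0.25 for 40 v 10 at 10–20% loss, with 76–78% power at the 0.21 noninferiority margin.
- **Report at full enrolment:** say that the figures assume complete follow-up, withdraw the statement in Settings and participants that 1200 allows for attrition, and correct the 40 v 10 figure (0.23 with the school as cluster).

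If the authors keep the group basis, they should state that it assumes negligible correlation between groups in the same school, say how control schools are treated, and give 0.215–0.225 for 40 v 10 after loss.

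The noninferiority margin should not be widened to restore 80% power. No extra enrolment is needed; the only cost is slightly less favourable stated figures.

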#### Data collection

Data collection will be at three levels: teacher, principal and youth. Teachers (*N* = 160) and principals (*N* = 40) will complete quantitative assessments on implementation-level outcomes at baseline and post-intervention. All principals and a subset of teachers (*N* = 40) will also complete qualitative exit interviews at post-intervention to explore key aspects of feasibility, acceptability, and adoption, (e.g., usefulness of YRI skill-building exercises), and internal and external factors that might influence facilitator experiences (e.g., school climate, incentives). The subset of teachers will be selected based on a multivariate sampling matrix [31, 32]. We will also explore feasibility and acceptability of mobile-based supervision via key informant interviews with facilitators who received mobile supervision at post-intervention.

Youth (*N* = 1200) will complete quantitative assessments on mental health and daily functioning at baseline and post-intervention. Youth from intervention schools (*N* = 960) will complete quantitative assessments on implementation-level outcomes. A subset of youth (from intervention schools; *N* = 32) randomly selected based on a multivariate sampling matrix will complete exit interviews at post-intervention to obtain their feedback on YRI feasibility, acceptability, and barriers/facilitators to adoption. We will also collect data on educational outcomes for all youth via administrative records (i.e., school attendance, grades, tardiness, disciplinary reports) at baseline, post-intervention and 12-month follow-up. All youth will complete the EQ-5D-3 L at baseline, post-intervention and 12-month follow-up to inform the cost-effectiveness analysis [33].

Trained RAs will administer assessments electronically via tablets. All classroom instruction, assignments and tests are completed in English in our catchment area, thus the Western region schools, assessments and interviews will be completed in English as a first option. Versions of all study assessments will also be available in Krio (the local language) for any participants indicating difficulties with English fluency or a preference for completing assessments in Krio. All measures have been forward and backward translated from English to Krio previously. We will report data disaggregated by sex.

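### The three detectable effects given for student outcomes cannot all hold together, and the 12-month wording beside them is broader than the data schedule

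*Protocol article*

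**What the plan says.** All three figures stand in one paragraph of the protocol article, under Statistical power analysis for student outcomes. It sets the assumptions at the start: "At a power of 0.8 and an alpha of" 0.05, "one-tailed to assess noninferiority), using an ICC of 0.03", the ICC being attached to the group and "based on prior ICCs for mental health outcomes of 0.01-0.04".

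- **Mobile v standard supervision (20 v 20 schools):** a detectable difference of 0.21, which also serves as the margin: "at a negative difference of 0.21 or smaller, mobile supervision will be considered noninferior to standard".
- **Either supervision model v control (20 v 10), one-tailed:** "we have 0.8 power to detect a standardized effect of 0.26".
- **Both models pooled v control (40 v 10):** "In a comparison of all 40 YRI schools as compared to the 10 control schools, the minimum detectable effect would be 0.21". Neither the tails nor any other assumption is restated.

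The paragraph opens with noninferiority on youth mental health and describes its calculation as "for comparisons at a single time point (post-intervention or 12-month follow-up) for student outcomes". Under Data collection, however, youth "will complete quantitative assessments on mental health and daily functioning at baseline and post-intervention". Only the EQ-5D-3L and the administrative school records are also scheduled at 12 months.

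**The concern.** With the same number of youth per school, a 40 v 10 split estimates a difference less precisely than a 20 v 20 split, because the 10 control schools dominate the variance. Yet the paragraph gives both the same detectable effect. At least one stated figure is therefore wrong, or rests on an assumption that differs from the others and is not disclosed.

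Two things are at stake. A reader cannot tell what power the comparisons with control have. And the 0.21 for 20 v 20 is also the noninferiority margin, so doubt about the calculation reaches a decision rule.

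The 12-month wording raises a smaller problem of the same kind: read with the paragraph's opening, it suggests power for mental health scales at a visit where they are not scheduled.

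**Working it through.** **Inputs.** Power 0.80, one-tailed alpha 0.05 and ICC 0.03 come from the power section. Settings and participants gives 24 youth per school, two groups per intervention school (so about 12 per group), 480, 480 and 240 youth in the three arms, and 10–20% attrition.

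**Step 1: a check that needs no ICC.** Let a be the variance of one 20-school arm mean and c that of the control mean. The three contrasts have variances 2a (20 v 20), a + c (20 v 10) and a/2 + c (40 v 10). With a common alpha, tail and power:

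MDES(40v10)² = MDES(20v10)² − MDES(20v20)²/4

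- Stated figures: 0.26² − 0.21²/4 = 0.0676 − 0.0110 = 0.0566; square root 0.238.
- Lowest value after rounding: √(0.255² − 0.215²/4) = 0.231.
- Highest value after rounding: √(0.265² − 0.205²/4) = 0.244.

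The stated 0.21 lies outside 0.231–0.244. This holds for any ICC, cluster unit, attrition rate or control-arm variance.

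With equal cluster structure in all arms, the effect scales with √(1/J1 + 1/J2), where J is the number of schools. Scaling from 20 v 20 gives 0.21 × √(0.125/0.100) = 0.235. Scaling from 20 v 10 gives 0.26 × √(0.125/0.150) = 0.237.

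**Step 2: direct calculation.** MDES = (1.645 + 0.842) × √[DE × (1/n1 + 1/n2)], with DE = 1 + (m − 1) × 0.03.

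School clusters (m = 24) have DE = 1.69; groups (m = 12) have DE = 1.33. One-tailed, no attrition:

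| Contrast | Stated | Schools of 24 | Groups of 12 |
|---|---|---|---|
| 20 v 20 (480 v 480) | 0.21 | 0.209 | 0.185 |
| 20 v 10 (480 v 240) | 0.26 | 0.256 | 0.227 |
| 40 v 10 (960 v 240) | 0.21 | 0.233 | 0.207 |

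School clusters reproduce the first two figures and not the third. Group clusters reproduce only the third.

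**Step 3: attrition.** With 10–20% loss, one-tailed:

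- School clusters: 0.215–0.223 (20 v 20), 0.264–0.273 (20 v 10), 0.24–0.25 (40 v 10).
- Group clusters: 0.215–0.225 for 40 v 10.

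**Step 4: power at 0.21 for 40 v 10.** For school clusters, the standard error is √[1.69 × (1/960 + 1/240)] = 0.0938, and Φ(0.21/0.0938 − 1.645) = 0.72. With 10–20% attrition it is 70% to 67%. For group clusters it is 81% with no attrition and 78% to 75% with 10–20%.

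**Step 5: search for a consistent basis.** Varying cluster unit (24 or 12), ICC (0.01, 0.03, 0.04), tails, attrition (0, 10, 20%) and z or t multipliers gives 72 combinations. None yields 0.21, 0.26 and 0.21 together. Mixing tails does: groups of 12 with no attrition give 0.209 and 0.255 two-tailed for the first two, and 0.207 one-tailed for the third. The text states one-tailed tests for the first two.

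**Step 6: the margin.** Power at a margin of 0.21 for 20 v 20 is 80% with school clusters and no attrition, and 78% to 76% with 10–20% attrition. With group clusters it is 88%, falling to 86% to 83%.

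**Step 7: the 12-month wording.** Data collection puts mental health and daily functioning at baseline and post-intervention, as does the Abstract. Quantitative analysis places the youth comparison at post-intervention. Only the EQ-5D-3L and school records extend to 12 months.

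**The case against.** The strongest reply is that the 40 v 10 figure may be the correct one. The protocol attaches the ICC to the group. Its Quantitative analysis section models students within YRI groups and expects no significant school-level ICC. On that reading, with no attrition, 40 v 10 is 0.207 and rounds to the stated 0.21; the other two figures are then merely conservative. A reader who concludes that the pooled effect simply is 0.235, and that power is 72% rather than 80%, has assumed that the ICC acts over 24 youth per school. The document does not say that, and this part of the reply stands.

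It does not remove the contradiction, since the other two figures then fail. It is also weakened on two counts. The sample is said to allow for 10–20% attrition, and with that loss the group-level figure is 0.215–0.225. And the two groups per school are described only for intervention schools: with groups of 12 in the YRI arms and school clusters of 24 in control, 40 v 10 is 0.228 with no attrition. Attrition does not rescue the school-level reading either, because its first two figures then also drift from those stated.

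On timing, the reply is that the sentence says student outcomes and names no scale. The EQ-5D-3L is listed among the youth mental health outcomes and is collected at 12 months, as are school records. That stands too: the documents do not support saying that no 12-month comparison can be run.

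**Conclusion.** The inconsistency is certain; which figure is wrong is not. Under a common alpha, tail and power, 0.21 and 0.26 force 40 v 10 to lie between 0.231 and 0.244. If those two stand, the pooled contrast has a detectable effect of about 0.235 and about 72% power at 0.21. If the ICC acts on groups of 12 with no attrition, 0.21 for the pooled contrast stands, and the other two should be about 0.185 and 0.227.

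A reader might infer that the trial's main test of the YRI is underpowered. The documents do not support this. Study design makes youth clinical outcomes secondary and says the control schools serve primarily the cost-effectiveness analysis, and the hypothesis on youth outcomes compares the two supervision models. Nor is the 0.21 margin shown to be wrong; it rests on a calculation whose basis is unclear.

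The 12-month wording is too broad for the DERS, HSCL, risk-behavior and WHO-DAS scales. It is sound for the EQ-5D-3L and educational outcomes.

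**What to change.** 1. State the cluster unit, tails and attrition once, and recompute all three figures on that basis. Changing only the pooled figure to 0.235 could introduce an error if the group is the intended unit. With school clusters of 24, one-tailed, the figures are 0.21, 0.26 and 0.23 with no attrition, and about 0.215–0.22, 0.26–0.27 and 0.24–0.25 with 10–20%.
2. Check the 0.21 noninferiority margin against the recomputed 20 v 20 figure. Say whether it was chosen in its own right or taken from the power calculation, and give the power at that margin.
3. Limit the 12-month wording in the power section to the EQ-5D-3L and educational outcomes.

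The cost is a few sentences and a short recalculation, with no change to the sample, schedule or conduct. Trial status reports that youth recruitment had not begun at submission.
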